Current international TB management guidelines (Nahid et al., 2016) endorse the first-line therapeutic regimen comprising rifampicin, isoniazid, pyrazinamide, and ethambutol (RIPE protocol), supplemented by oxygen therapy in cases of concurrent obstructive ventilatory impairment. However, extended administration of first-line anti-TB agents precipitates dual therapeutic challenges: cumulative drug resistance development and suboptimal COPD comorbidity control. Therapeutic escalation to second-line agents (fluoroquinolones, diarylquinolines, and nitroimidazole derivatives including moxifloxacin, bedaquiline, and pretomanid) becomes imperative for multidrug-resistant TB. Nevertheless, pharmacovigilance data reveal significant neurotoxicity and idiosyncratic hepatotoxicity associated with prolonged use (Johnson et al., 2024). This therapeutic dichotomy has revitalized interest in TCM as adjuvant therapy, with meta-analytical evidence demonstrating adjunctive TCM protocols significantly improve clinical outcomes through three principal mechanisms: (1) reduction of standard chemotherapy cycle (2) accelerated sputum culture conversion rates and (3) decreased recurrence risk. Furthermore, longitudinal studies reveal TCM’s immunomodulatory properties mediate sustained pulmonary rehabilitation, such as enhance patient immunity and improve lung function (Luo and Cai, 2019; Huang and Hu, 2017).

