Yiqi Gubiao Pill, a hospital-developed botanical formulation (Preparation Approval No. ZJ20130098; National Invention Patent License ZL201410536529.5; NMPA Clinical Trial Authorization 2018L02421), demonstrates multimodal therapeutic properties in preclinical studies. Pharmacodynamic evaluations reveal its significant antitussive, antiasthmatic, mucoactive, and immunopotentiating effects, with mechanistic studies indicating Yiqi Gubiao Pill’s capacity to downregulate serum concentrations of pro-inflammatory cytokines (Li et al., 2016). Bronchodilatory effects are mediated through reduction in airway resistance (Raw) and upregulation of pulmonary aquaporin-1 (AQP1) expression, elucidating its molecular mechanism in respiratory pathophysiology. This clinical trial (ClinicalTrials.gov ID: NCT06676800) implements a prospective double-blind, placebo-controlled randomized clinical trial (RCT) design to evaluate both therapeutic efficacy and safety profile in treatment-naive adults with active PTB complicated by COPD. This evidence-based approach aims to establish optimized integrative management protocols for this high-risk patient cohort. Meanwhile, through this three-phase model of “local problem-driven, scientific method validation, global demand adaptation,” Xinjiang’s TB research outcomes can serve as a pivotal nexus connecting China’s expertise with global tuberculosis control initiatives.

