### 2.3 Participants

#### 2.3.1 Inclusion criteria

Patients who meet the following criteria will be included:1. Aged 40-75 years old;2. Meeting the Western medical diagnostic criteria and typing standards for active PTB;3. No use of steroids, anti-tuberculosis medications, or immunosuppressants, nor desensitization therapy administered within the past month;4. Documented comprehension of therapeutic protocols with voluntarily signed informed consent.

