#### 2.5.2 Conventional treatment

Both treatment and control groups receive standardized anti-tuberculosis therapy following the WHO-recommended RIPE regimen—an intensive 8-week phase with daily rifampicin, isoniazid, pyrazinamide, and ethambutol, followed by a 16-week continuation phase with rifampicin and isoniazid—and concurrently receive guideline-concordant COPD management, including maintenance bronchodilator therapy.

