## 3 Discussion

Tuberculosis remains a critical global public health threat, with its disease burden and therapeutic complexity exhibiting amplified effects in specific regions. Approximately one-third of the global population harbors latent Myc infection, forming a vast reservoir for potential active disease, while the emergence of comorbidities further complicates clinical management. In Northwest China, for instance, disparities in geographic conditions and healthcare resource allocation have fostered a region-specific TB epidemic pattern. The synergistic interaction between TB and chronic airway diseases accelerates pulmonary function decline and drastically diminishes quality of life. Although current international standardized regimens effectively suppress pathogen proliferation, prolonged drug exposure risks driving antimicrobial resistance, and inadequate control of comorbidities creates dual therapeutic barriers. Against this backdrop, traditional medicine offers novel perspectives through immunomodulatory mechanisms and pathological microenvironment repair, which may enhance treatment tolerance, alleviate symptoms, and reduce relapse rates.

This randomized controlled trial represents a pivotal effort to address the dual burden of active PTB complicated by secondary COPD in Xinjiang—a region disproportionately affected by TOPD. By integrating standardized anti-TB chemotherapy with Yiqi Gubiao Pill, the study design reflects a holistic approach to managing this high-risk population. This strategy could reduce reliance on prolonged first-line anti-TB regimens, potentially delaying or avoiding the need for more toxic second-line drugs. If validated, these findings would provide critical insights for optimizing TOPD treatment strategies, particularly in resource-constrained settings with systemic healthcare challenges.

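### The Introduction describes a treatment-naive population, but the printed criteria admit previously treated patients and do not exclude TB already known to be drug-resistant

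*Protocol article*

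**What the plan says.** **Population described.** The Introduction (section 1) states that the trial evaluates efficacy and safety in "treatment-naive adults with active PTB complicated by COPD".

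**Population admitted.** Section 2.3.1 lists four inclusion criteria. Item 2 is "Meeting the Western medical diagnostic criteria and typing standards for active PTB". Item 3 is "No use of steroids, anti-tuberculosis medications, or immunosuppressants, nor desensitization therapy administered within the past month". The five exclusions in section 2.3.2 cover other lung disease, severe organ disease, psychiatric disorders, neoplasms and immunodeficiency. None mentions earlier TB treatment or drug resistance. Section 2.2 asks for CT evidence of active lesions, a positive smear and culture growth, under a national standard that is cited but not reproduced.

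**Background therapy.** Section 2.5.2: "Both treatment and control groups receive standardized anti-tuberculosis therapy following the WHO-recommended RIPE regimen". It sets 8 weeks of four drugs, then 16 weeks of rifampicin and isoniazid, and states no alternative regimen.

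**The article's own view of resistance.** The Introduction says that escalation to second-line agents "becomes imperative for multidrug-resistant TB", and it names "cumulative drug resistance development" as a consequence of extended first-line treatment. The Discussion (section 3) repeats that "prolonged drug exposure risks driving antimicrobial resistance".

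**The concern.** A treatment-naive population and a population off treatment for a month are different populations. The second includes relapses, treatment failures and interrupted courses. The article links resistance to extended drug exposure, so by its own reasoning these added patients are the ones in whom resistance is more to be expected.

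Two things are at stake. The first is what the result can be said to apply to: a report that repeats the Introduction's description would be wrong if previously treated patients had been enrolled. The second is the fit between eligibility and background therapy. The comparison is of pill against placebo on top of one fixed regimen, and that regimen should be suitable for everyone who can enter. As printed, a patient already known to have multidrug-resistant TB meets the criteria of a trial whose only stated regimen the authors themselves regard as insufficient for that disease.

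**Working it through.** No figure in the article bears on this point, so the check is a comparison of statements.

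**Step 1. Does item 3 amount to treatment-naive?**

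| Patient at screening | Treatment-naive (section 1) | Meets item 3 (section 2.3.1) | Removed by section 2.3.2 |
|---|---|---|---|
| Never treated for TB | yes | yes | no |
| Relapse after a course completed more than a month ago | no | yes | no |
| Failed or stopped treatment more than a month ago | no | yes | no |
| Anti-TB drugs within the month | no | no | not needed |

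Rows two and three show the conflict: these patients can be enrolled but do not fit the description. Both statements stand in the current text, so one has to change whatever a fuller protocol contains.

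**Step 2. Do the exclusions fit the fixed background?**

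- Section 2.5.2 gives RIPE to both groups and states no exception.
- Section 1 holds that multidrug-resistant TB requires second-line agents.
- Section 2.3.2 has five items, and none removes known resistance.
- Section 2.2 lists CT, smear and culture growth. These establish active TB and do not by themselves sort cases by resistance.
- The standards named in sections 2.2 and 2.3.1 are not shown. They may classify resistance, although classifying a case does not exclude it.

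On the printed text alone, known resistance is compatible with entry. The unseen standards make this step weaker than Step 1.

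**Step 3. How many patients?** The article gives no rate of earlier treatment or of resistance. The planned enrolment in section 2.4 is 74, so each patient outside the description is 1/74 = 1.4% of the sample. The count itself cannot be derived.

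**Step 4. What kind of error is it?** Earlier treatment and resistance known at screening are baseline characteristics. Randomisation balances them between the arms in expectation, so admitting such patients does not bias the comparison of pill with placebo. What changes is whom the result describes and whether the stated background suits all of them.

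**The case against.** **Grammar.** The one-month limit in item 3 could be attached to desensitization therapy alone, so that anti-TB drugs would be barred without a time limit and the two statements would agree. That reading would also bar anyone who had ever taken a steroid or an immunosuppressant, which is not a plausible rule for adults aged 40 to 75 with obstructive lung disease. It does show that the sentence needs repair.

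**Introduction against Methods.** Inclusion item 3 governs enrolment and the Introduction only describes. This is true, and it is why the severity is low. It does not make the description correct.

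**A condensed article.** The inclusion list is visibly shortened: comorbid COPD appears in section 2.2 but not among the numbered criteria. Silence about resistance is therefore not proof that resistant TB is admitted, and the cited standards may deal with it. This stands, and the second point is weaker because of it. It does not touch the first, which rests on two printed statements.

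**Stronger readings.** A reader might infer three further things that the document does not support.

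- That susceptibility testing is missing. A condensed article may leave it to the full protocol.
- That patients with known resistance would be kept on RIPE. Nothing in the article forbids a clinician from changing therapy.
- That rejection item 3 in section 2.3.3 would remove a randomised patient whose anti-TB regimen has to change, with loss of power or an imbalance between the arms. That item concerns concomitant medication, whereas anti-TB drugs are background treatment under section 2.5.2. It does not name second-line drugs or say which analysis a rejected patient leaves. The Discussion's phrase "potentially delaying or avoiding the need for more toxic second-line drugs" expresses a hope and does not forecast switches during the 12 weeks of study treatment.

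**Conclusion.** The point holds in two parts of unequal strength.

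1. The described population and the population that can be enrolled differ. The printed text establishes this, given the natural reading of item 3 as a one-month limit on all the drugs it lists.
2. No printed exclusion removes TB already known to be drug-resistant, although RIPE is the only stated regimen and the article holds that multidrug-resistant disease needs second-line drugs. This is probable rather than certain, because it assumes that the unseen diagnostic and typing standards do not already exclude such patients.

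Severity is minor. The number of affected patients is unknown, and no effect on power or on the estimated difference is claimed. The consequence is for who is enrolled and for the population to which the conclusion applies.

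**What to change.** Two changes of wording, by amendment.

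1. Make sections 1 and 2.3.1 agree. Either change inclusion item 3 to require no previous anti-TB treatment, with the one-month limit kept as a separate item for steroids, immunosuppressants and desensitization therapy; or drop treatment-naive from the Introduction and describe the population as having had no anti-TB treatment in the past month. The first choice keeps the stated population. The second keeps recruitment wider and makes the next change more important.
2. Add to section 2.3.2 an exclusion for rifampicin-resistant or multidrug-resistant TB known at screening, so that those enrolled fit the regimen in section 2.5.2. If the cited standards already have this effect, a sentence saying so is enough.

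No new test and no new regimen is proposed. The cost is a few candidates lost at screening, more if any previous treatment is excluded. The second change reaches only resistance known at screening.

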#### 2.3.2 Exclusion criteria

Patients who meet any of the following criteria will be excluded:1. Patients with pneumothorax, pleural effusion, lung cancer, or other severe pulmonary comorbidities;2. Patients with severe cardiovascular/cerebrovascular, hepatorenal, or hematopoietic system disorders;3. Patients with psychiatric disorders;4. Patients with neoplastic diseases;5. Patients with congenital or acquired immunodeficiency.

#### 2.3.3 Rejection criteria

1. Patients with documented non-adherence to prescribed medication regimens, precluding reliable therapeutic effect assessment;2. Patients withdrawing from the trial during the study period through self-initiated or legal guardian-requested discontinuation;3. Patients using concomitant medications outside the approved trial protocol, particularly agents known to compromise trial integrity or confound efficacy assessments.

#### 2.3.4 Corresponding treatment for dropout and loss to follow-up cases

1. Upon occurrence of serious adverse events requiring physician-directed trial discontinuation, such cases shall be classified as treatment failures;2. Disease progression during the trial period or emergence of confounding symptoms compromising outcome assessments, when leading to investigator-initiated termination, shall be categorized as therapeutic non-responders;3. Protocol deviations exceeding acceptable thresholds (e.g., medication adherence poor) precluding reliable efficacy evaluation shall be excluded;4. Cases where unblinding or emergency unblinding occurs during the trial.

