### 2.6 Outcome

#### 2.6.1 Primary outcome

Lung function, long-term lung function decline and quality of life were established as primary efficacy endpoints.

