##### 2.6.1.3 ​​Quality of life (QL) evaluation​​

QL was assessed using validated tools:① COPD Assessment Test (CAT)​​: An eight-item questionnaire scoring symptoms (cough, dyspnea) and functional limitations (0–40 scale). A 5-point change indicates clinically meaningful improvement.② mMRC Dyspnea Scale​​: Grades breathlessness from 0 (no dyspnea) to 4 (dyspnea at rest). Scores ≥2 correlate with increased hospitalization risk.③ Baseline Dyspnea Index (BDI)​​ and ​​Transition Dyspnea Index (TDI)​​: BDI assesses dyspnea impact on daily activities (e.g., task difficulty), while TDI measures changes post-treatment. A TDI score ≥1 signifies meaningful improvement.​​④ Chest Radiography​​: Screened for structural abnormalities (e.g., hyperinflation, effusions) but limited in detecting early small airway disease.​​⑤ High-Resolution CT (HRCT)​​: Quantified emphysema extent, airway wall thickness, and fibrosis patterns. Dynamic CT evaluated ventilation-perfusion mismatches in advanced cases.⑥ Acute Exacerbation of COPD (AECOPD): Exacerbation Frequency Classification: Based on events in the previous 12 months. Infrequent exacerbators: ≤1 exacerbation/year without hospitalization; Frequent exacerbators: ≥2 exacerbations/year or ≥1 requiring hospitalization.

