#### 2.6.2 Secondary outcomes

Secondary outcomes will include TCM syndrome differentiation scoring, implemented per the Guidelines for Clinical Research of New Chinese Medicines (Trial). Symptomatology is categorized as follows: Core symptoms: Graded 0 (absent), 2 (mild), 4 (moderate), 6 (severe); Ancillary symptoms: Graded 0 (absent), 1 (mild), 2 (moderate), 3 (severe); Non-scored elements: Tongue manifestation and pulse characteristics. The composite TCM syndrome score is calculated through summation of all graded symptom scores.

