### 2.8 Data analysis

Two researchers independently entered observational data to establish a standardized database, with subsequent statistical analyses performed using SPSS 25.0. Quantitative variables exhibiting normal or approximately normal distributions are expressed as mean ± standard deviation (x̄±s). Between-group comparisons of means were analyzed via independent t-tests, while within-group longitudinal changes were assessed using paired t-tests. Categorical data were evaluated through χ^2^ tests or Wilcoxon rank-sum tests, and ordinal data were analyzed using non-parametric methods (e.g., Kruskal-Wallis test for multi-group comparisons). All statistical inferences employed two-tailed tests with a predefined significance threshold of α = 0.05.

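### The failure and non-responder labels for patients stopped for SAEs or progression match no defined outcome, so they enter no stated analysis and these patients may be left out of the comparisons of means

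*Protocol article*

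**What the plan says.** Section 2.3.4 of the protocol article sets separate rules for patients who do not complete.

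- Item 1, SAE stops: "Upon occurrence of serious adverse events requiring physician-directed trial discontinuation, such cases shall be classified as treatment failures".
- Item 2, progression or confounding symptoms: these cases, "when leading to investigator-initiated termination, shall be categorized as therapeutic non-responders".
- Item 3, serious protocol deviations such as poor adherence: those "precluding reliable efficacy evaluation shall be excluded".

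The outcomes are set in section 2.6. Section 2.6.1 states: "Lung function, long-term lung function decline and quality of life were established as primary efficacy endpoints". Under these headings come spirometric values, annual decline, the CAT, mMRC, BDI and TDI scores, imaging and exacerbation frequency. The secondary outcome in section 2.6.2 is a total: "The composite TCM syndrome score is calculated through summation of all graded symptom scores".

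Some cut-offs are given. FEV1 decline is classed by mL per year, and a 5-point CAT change is called clinically meaningful. For the TDI, "A TDI score ≥1 signifies meaningful improvement".

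The analysis is in section 2.8: "Between-group comparisons of means were analyzed via independent t-tests". Categorical data go to χ² or Wilcoxon tests, but no response or failure variable is named.

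**The concern.** Calling a patient a failure or a non-responder settles how that patient counts only if the endpoint is success or failure. Here the label meets measured values and summed scores. A t-test of FEV1% or CAT needs a number for each patient, and the label supplies none.

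The evident purpose of items 1 and 2 is to count bad outcomes against the arm in which they occur. If the label leads nowhere and later values are absent, a default analysis does the reverse: it leaves out patients who probably did worst. With more such stops in one arm, that arm's mean is flattered on the primary endpoints.

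**Working it through.** **1. Do the labels reach any stated analysis?**

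| Place in protocol article | What it fixes | Link to the labels |
|---|---|---|
| 2.6.1.1 | FVC, FVC%, FEV1%, FEV1/FVC | none |
| 2.6.1.2 | annual decline; rapid, moderate and physiological classes | none; needs observed spirometry |
| 2.6.1.3 | CAT, mMRC, BDI/TDI, imaging, exacerbations; CAT and TDI cut-offs | none |
| 2.6.2 | summed TCM score | none |
| 2.8 | t-tests for means; χ² or Wilcoxon for categories | none |

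The labels reach no stated comparison.

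**2. Where does omission follow from the text?** Section 2.6.1.2 admits to the decline analysis only patients with at least three valid tests over 12 months. On the Table 2 schedule, a patient who leaves the trial in week 5 has at most two tests (baseline and month 1). That patient is a failure under 2.3.4 and outside a primary endpoint under 2.6.1.2. For the other endpoints, omission is a possibility, not a stated rule.

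**3. Size if they are omitted.** Score outcomes so that higher is better. Let a share p of an arm be dropped, with outcomes δ worse than those retained (mean m).

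- Mean of all randomised in the arm: (1 − p)·m + p·(m − δ) = m − pδ.
- Mean of those retained: m, too favourable by pδ.
- Bias in the difference, with the same δ in both arms: (p_active − p_control)·δ.

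The documents give neither p nor δ, so both are assumed:

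- 5-point imbalance, δ = 0.5 SD: 0.05 × 0.5 = 0.025 SD.
- 15-point imbalance, δ = 1 SD: 0.15 × 1 = 0.15 SD.
- Equal shares: 0 × δ = 0.

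**4. Scale.** Section 2.4 gives 31 per group but no effect size, SD or power, so that figure cannot be reproduced. At an assumed 80% power and the stated two-sided 0.05, the detectable difference is (1.96 + 0.84) × √(2/31) ≈ 0.71 SD. The range in step 3 is then 0.025/0.71 ≈ 3.5% to 0.15/0.71 ≈ 21% of it.

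**5. Effect on the test.** This was simulated with 20,000 runs, 37 randomised per arm, no net effect among all randomised, δ = 1 SD and the labelled patients dropped. The chance of a significant result favouring the pill is nominally 2.5%.

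| Share dropped, pill vs placebo | Bias (SD) | Chance of significance favouring the pill |
|---|---|---|
| 5% vs 5% | 0 | 2.5% |
| 10% vs 5% | 0.05 | 3.9% |
| 15% vs 5% | 0.10 | 5.8% |
| 20% vs 5% | 0.15 | 8.8% |

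**The case against.** The strongest reply is that carrying a discontinuation label into a continuous endpoint is ordinary SAP work, and the SAP is not shown. This stands in part: an unseen plan may contain a rule. But the article does more than stay silent. It states a rule, and that rule does not fit the endpoints and tests stated beside it.

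Three stronger readings are tempting and not supported.

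- A reader might infer that the plan removes these patients from every comparison. It does not say so. In section 2.3.4 the wording of exclusion belongs to item 3, and the contrast suggests that items 1 and 2 are meant to stay in. Section 2.4 also names intent-to-treat, though only as a sample-size aim. Trial discontinuation makes missing later values plausible, but no passage says that visits end.
- A reader might infer that no outcome has categories at all. Sections 2.6.1.2 and 2.6.1.3 contain several, and section 2.8 has tests for them. What is missing is any link from the labels to those categories.
- A reader might infer a conflict because item 1 covers SAEs of any cause while section 2.6.3 deals with SAEs due to the trial medication. Section 2.6.3 governs reporting and stopping, whereas item 1 is an efficacy classification. Both arms receive the same anti-tuberculosis regimen, and counting SAEs regardless of cause treats the arms alike.

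It is also fair to say that the upper end of the range is demanding. Fifteen points of 37 is 0.15 × 37 ≈ 5.6 patients, while the anticipated 20% dropout from all causes is 0.20 × 37 ≈ 7.4 per arm.

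**Conclusion.** The point holds as a mismatch between a stated rule and the stated endpoints. The labels in items 1 and 2 enter no stated analysis. The patients concerned may be omitted from the comparisons of means, and early stoppers with fewer than three tests are left out of the decline analysis by rule.

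The resulting bias is 0.025 to 0.15 SD under assumed imbalances of 5 to 15 points and gaps of 0.5 to 1 SD, favouring the arm with more such stops. It is zero if shares and gaps are equal. These rates and gaps are assumptions, and the calculation takes omission as given. The issue deserves correction before unblinding because it touches primary endpoints, but its likely size is moderate and it does not by itself undermine the trial.

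**What to change.** In items 1 and 2 of section 2.3.4, state that spirometry, CAT and the other scores continue to be collected at the visits already scheduled in Table 2 after the pill is stopped, and that all measured values are analysed in the randomised arm.

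Add a responder summary on the cut-offs already given (CAT improvement of at least 5 points, TDI of at least 1). Count SAE stops, progression stops and deaths as non-responders, and compare arms by the χ² test already planned. Label it supportive, not an additional primary endpoint. Report the number of such stops by arm.

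The cost is a few lines of protocol wording and two extra tables, with no extra patients and no new scheduled visits. There are two downsides. The estimated effect may shrink because poor outcomes stay in. Patients who die or refuse further visits are still missing from the means, so the responder summary covers them on CAT and TDI but not on spirometry.

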##### 2.6.1.2 Long-term lung function decline

Long-term decline in lung function will be evaluated through serial spirometry conducted at baseline and predefined follow-up intervals (every 3 months). Patients with at least three valid pulmonary function tests over a 12- month period will be included in the analysis of decline trajectory. The following parameters will be used to quantify and classify lung function deterioration:① Annual FEV_1_ Decline (mL/year): The change in forced expiratory volume in 1 s (FEV_1_) over time will be calculated and expressed per year. A decline greater than 60 mL/year will be defined as “rapid decline,” in alignment with thresholds reported in GOLD and SPIROMICS cohorts. Declines between 30 and 60 mL/year will be considered moderate, while declines under 30 mL/year will reflect physiological aging.② Annual Change in FEV_1_% Predicted: The annual reduction in FEV_1_ as a percentage of predicted values will be computed. A reduction exceeding 5% per year will indicate clinically significant progression.③ FVC and FVC% Predicted Trends: Longitudinal changes in forced vital capacity (FVC) and its percentage of predicted will be monitored to detect potential restrictive patterns or lung volume loss.④ FEV_1_/FVC Ratio Decline: The ratio of FEV_1_ to FVC will be tracked over time. A progressive decrease in this ratio will reflect worsening airflow obstruction, particularly relevant in COPD progression.

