#### 2.6.3 Safety assessment and adverse events reporting

An independent Data Safety Monitoring Board (DSMB)—comprising a pulmonologist, a clinical pharmacologist, and a biostatistician with no study roles—will oversee participant safety. The DSMB will review aggregate safety data at predefined intervals and *ad hoc* as needed, operating under a written charter with prespecified review procedures, communication pathways, emergency unblinding procedures, and stopping rules.

Safety surveillance will involve serial biochemical monitoring during pre-treatment, on-treatment, and post-treatment phases to establish the safety profile of Yiqi Gubiao Pill. All adverse events occurring during the study period will be prospectively monitored and systematically documented. Participants will be instructed to self-report potential adverse events in real-time, and researchers will determine whether the event is related to the study medication. If the adverse event is related to the study formulation, it is then referred to as a side effect. If the side effects are mild and the patient agrees to continue the treatment, medication will be continued after the symptoms have subsided. In case of serious adverse events due to the trial medication, the researcher will report to the DSMB and research ethics committee within 24 h, ask the patient to discontinue the medication, and implement emergency safety measures.

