### 2.7 Data collection and management

Data collection will be carried out before, during, and after treatment (Table 2). Data will be recorded on pre-designed case report forms (CRF) and transferred to an electronic format (RevMan 5.3) for storage and data backup. All patient identity information will be encoded.

**TABLE 2 T2:** Participant enrollment process, interventions, and outcome measures.

Items	Baseline	Treatment phase (monitor monthly)			Follow-up phase (monitor monthly)		
		1 month	2 months	3 months	3 months	6 months	12 months
Enrolment							
Recruitment	●						
Eligibility Screening	●						
Signed written informed consent	●						
Allocation	●						
Intervention							
Yiqi Gubiao pill (Treatment group)		●	●	●	●	●	●
Yiqi Gubiao pill Placebo (Control Group)		●	●	●	●	●	●
Outcomes							
forced vital capacity (FVC)	●	●	●	●	●	●	●
the percentage of FVC predicted (FVC%)	●	●	●	●	●	●	●
the percentage of forced expiratory volume in one second predicted (FEV1%)	●	●	●	●	●	●	●
FEV1/FVC	●	●	●	●	●	●	●
CAT score	●	●	●	●	●	●	●
mMRC score	●	●	●	●	●	●	●
BDI score	●	●	●	●	●	●	●
TDI score	●	●	●	●	●	●	●
chest X-ray/CT	●	●	●	●	●	●	●
Traditional Chinese Medicine Symptom (TCMS) score	●	●	●	●	●	●	●
Security							
All adverse events (including symptoms, signs, etc.)		●	●	●	●	●	●
Liver function: alanine aminotransferase, aspartate aminotransferase, total bilirubin, albumin, globulin	●	●	●	●	●	●	●
Renal function: uric acid, urea nitrogen, serum creatinine, β2-microglobulin, urinary protein, carbon dioxide binding rate, cystatin C	●	●	●	●	●	●	●

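### Section 2.3.4 does not separate stopping the medication from leaving the trial, so patients who exit early after an SAE or progression are likely to be missing from the long-term decline primary endpoint

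*Protocol article*

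**What the plan says.** Section 2.3.4 of the protocol article sets out how dropouts and losses to follow-up are handled. Item 1 concerns "serious adverse events requiring physician-directed trial discontinuation, such cases shall be classified as treatment failures". Item 2 concerns disease progression and a second case: "emergence of confounding symptoms compromising outcome assessments, when leading to investigator-initiated termination, shall be categorized as therapeutic non-responders". Item 3 treats serious protocol deviations differently: cases "precluding reliable efficacy evaluation shall be excluded". Patients under items 1 and 2 are therefore to be counted as unfavourable, not excluded.

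Section 2.6.1 makes long-term lung function decline one of three primary endpoints. Section 2.6.1.2 measures it by spirometry at baseline and every 3 months, and limits the analysis: "Patients with at least three valid pulmonary function tests" over 12 months are included. Table 2 (section 2.7) also lists spirometry at months 1, 2 and 3 of treatment and at follow-up visits to 12 months.

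Section 2.4 sizes the trial at 31 per group, 74 in total after allowing for 20% dropout, and refers to an intent-to-treat analysis. Section 2.6.3 says that "All adverse events occurring during the study period will be prospectively monitored and systematically documented" and that a patient with a drug-related SAE is asked to stop the medication.

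**The concern.** Stopping a trial drug and leaving a trial are different events. A patient who stops the pills because of an SAE or progression can still attend for spirometry, and that patient's later lung function is part of what the randomised comparison should measure. Section 2.3.4 merges the two events. It speaks of discontinuing the trial and of termination, under a heading about dropout, and nothing in the article says that visits go on afterwards.

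If visits do end, the three-test rule in section 2.6.1.2 removes the earliest of these patients from the decline analysis. Those who leave because their disease progressed would be absent from the endpoint that measures progression. The absence is related to outcome and may differ between arms. The arm that loses more such patients looks better than it should. That works against the pill if placebo patients progress more, and in its favour if the pill causes more SAE exits. Spirometry that was never done cannot be recovered by a later analysis plan, so the point has to be settled in the conduct of the trial.

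**Working it through.** The plan attaches no figure to this rule, so there is none to reproduce. The 31 per group in section 2.4 comes without an effect size, SD or power, so power is assumed below.

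**Step 1. Tests available at exit**, counting a test due in the exit month as done.

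| Exit at month | 3-monthly schedule (2.6.1.2): 0, 3, 6, 9, 12 | Table 2: 0, 1, 2, 3, then follow-up |
|---|---|---|
| 1 | 1 | 2 |
| 2 | 1 | 3 |
| 3 | 2 | 4 |
| 5 | 2 | at least 4 |
| 6 | 3 | at least 4 |

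On the 3-monthly schedule, any exit before month 6 leaves at most two tests, and that covers the whole 12-week treatment period. On Table 2, only an exit before month 2 does so. The 3-monthly interval and the 12-month span in section 2.6.1.2 favour the first reading. An annual slope from two or three months of data would also be very imprecise.

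**Step 2. Bias between arms.** Let *p* be the share of an arm lost and *d* the deficit of lost patients against those retained, in SD, taken as equal in both arms. The retained mean exceeds the mean of all randomised patients by *d* × *p*. The bias in the difference is therefore *d* × (*p*₁ − *p*₂). Each arm has 74/2 = 37 patients. Assume *d* = 0.5 to 1.0.

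- Equal losses: 0.
- One extra exit, 1/37 = 0.027: 0.5 × 0.027 = 0.014 to 1.0 × 0.027 = 0.027 SD.
- Two extra, 2/37 = 0.054: 0.027 to 0.054 SD.
- Ten points more, 0.10 × 37 = 3.7 patients: 0.05 to 0.10 SD.

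**Step 3. Against the detectable effect.** For a two-sided t-test at 0.05 (section 2.8) with 31 per group, the detectable effect is 0.723 SD at an assumed 80% power and 0.837 SD at 90%. For a ten-point difference, the bias is 0.05/0.837 = 6% to 0.10/0.723 = 14% of that effect.

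**Step 4. Effect on the test.** With no true effect, the noncentrality is bias × √(31/2): 0.05 × 3.94 = 0.20 and 0.10 × 3.94 = 0.39. On 60 degrees of freedom the two-sided rejection rate rises from 5.0% to 5.4% and 6.7%.

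**Step 5. Sharper selection, by simulation on assumed slopes** (control mean −60 mL/year, SD 100, true benefit 40 mL/year).

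- If 80% of patients with a slope below −160 or −120 mL/year exit, losses are 12.7% v 6.5% and 21.9% v 12.7% (control v active). The difference among those retained falls to 30.4 and 28.0 mL/year, a shift of 9.6/100 = 0.10 and 12.0/100 = 0.12 SD against the pill. With no true benefit the same rule gives no bias, because both arms lose the same share.
- If the exits are exactly the steepest decliners, 20% of control v 5% of active, a true 40 becomes about 16 and a true 0 becomes about −24, a shift of 0.24 SD.

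The documents support none of these inputs. They show only the range.

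**The case against.** The strongest reply is that section 2.3.4 is a classification rule. It says how a case is counted once a physician or investigator has ended it, and does not order anyone out. That stands. A reader might infer that an SAE or a confounding symptom obliges the investigator to terminate the patient, but item 2 applies only where termination has followed, so the text does not support that reading.

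The end of assessments is also inferred. Section 2.6.3 speaks of stopping the medication, Table 2 lists visits to 12 months without an exception for these patients, and a condensed article may leave continued follow-up to the full protocol. A reader might take the plan to say that visits stop; it does not say so. Against this, the words chosen in section 2.3.4 and its heading point to leaving the trial, and one sentence would settle it.

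A reader might further infer that the failure and non-responder labels are void because no listed outcome uses them. That goes too far. The decline classes in section 2.6.1.2, the COPD Assessment Test threshold ("A 5-point change indicates clinically meaningful improvement") and the chi-square tests in section 2.8 could take such labels. Linking them is ordinary work for an analysis plan that is not shown here. Counting these exits as unfavourable is conservative in intent.

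Finally, the exclusion itself comes from the three-test rule and does not reach every early exit. That also stands: it holds before month 6 or before month 2, depending on the schedule.

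**Conclusion.** The point holds in a limited form. Section 2.3.4 handles SAE and progression exits as dropouts without separating the drug from the trial. If assessments end there, as the wording suggests, the earliest of these patients are missing from a primary endpoint for outcome-related reasons. That does not sit with the intent-to-treat aim in section 2.4.

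The number of patients affected is not given, and the bias can go either way. On a deficit of 0.5 to 1.0 SD and a difference in exits of up to ten points it runs from 0 to about 0.10 SD, and it is nil if the arms lose the same share with the same deficit. The 0.24 SD case needs a 15-point difference made up only of the steepest decliners, and should not be read as an expected size. This is a cheap improvement to make, not a flaw that undermines the trial.

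**What to change.** Amend section 2.3.4 along these lines: *An SAE, disease progression or intercurrent symptoms may lead to the trial medication being stopped, but do not by themselves end participation. The remaining Table 2 assessments continue to the 12-month visit unless the patient withdraws consent or a test is clinically unsafe for that patient. These data are analysed in the randomised arm.* The failure and non-responder classifications can stay for any responder analysis that the analysis plan defines.

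The cost is a wording amendment and one case report form field that separates medication stopped, consent withdrawn and test unsafe. The visits are already in Table 2. The downside is some effort to retain patients who are off medication. Patients who withdraw consent or cannot be tested safely may still fall short of three tests, so the change reduces the gap without closing it.
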